### Design of the randomised evaluation

The impact evaluation will be an integral component of the monitoring and evaluation activities of the GFSP. Two rounds of surveys are envisioned, with the baseline planned in the intervention and control sites in June 2013 and a follow-up planned in November 2015. After the follow-up survey, the control schools and community will be fully integrated in the intervention. We will consider the possibility of conducting further surveys in the following years, building matched control groups in order to detect long-term effects of the intervention on smallholder agriculture.

The GSFP will be expanded across the 10 regions of the country. The GSFP has set clear criteria for the selection of the intervention areas as captured in the retargeting exercise conducted in 2012. Poverty rankings were developed using the Ghana Living Standards Survey and Core Welfare Indicators Questionnaire carried out in 2005/2006 and 2003 respectively. Food consumption scores were calculated using the Comprehensive Food Security and Vulnerability Assessment 2008/2009 and spatial data variables computed by the World Food Programme (WFP). The data were then used to generate district-level composites for share of national poverty and food insecurity that were then used to allocate programme resources.

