### Country context

Ghana is a lower-middle income country with a population of 25 million people, over 40 % of whom are under 15 years of age [3]. Despite the high rates of economic growth occurred in the past two decades, Ghana is ranked 138th in the 2014 Human Development Index table, with a life expectancy at birth of 61 years, 7 mean years of schooling for adults and a Gross National Income (GDP) based on per capita purchasing power parity (PPP) of US$3532 [4]. The domestic economy is centred on subsistence farming, which accounts for nearly 40 % of the GDP and employs over 50 % of the workforce [5]. Around 25 % of the country’s population live in poverty based on the national-level poverty line, with this percentage increasing to 38 % in rural areas in contrast to 10 % in urban ones [6]. Food security in the marginal agricultural and arid areas varies with the seasons. The peak hunger seasons for the south of Ghana are from May to August whereas the north of Ghana experiences peak hunger seasons between July and October. The incidence of malnutrition in Ghana has been assessed through the Ghana Demographic and Health Surveys (GDHS) conducted every 5 years since 1988. From 1993 to 2008 there was some progress in reducing the rate of chronic malnutrition, with rates of stunting decreasing from 34 % to 29 % [6]. According to the 2003 and 2008 GDHS the prevalence of anaemia among children of 6–59 months of age increased marginally from 76 % in 2003 to 78 % in 2008. In 2008, the prevalence of anaemia among rural children aged under 5 years (84 %) was higher than in urban areas (68 %). The overall prevalence of stunting among school-aged children was 17 %, ranging from 13 % in the forest-savannah transitional zone to 21 % in the northern savannah [6]. The same study estimated that the prevalence of anaemia among school-aged children was 39 %. This, however, varied widely across ecological zones. Anaemia rates were highest in the northern savannah (65 %) and the coastal savannah zones (59 %) and least prevalent in the transitional zone (16 %).

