### Methods of analysis

The randomised design allows for the identification of causal impacts of interventions using comparisons of mean outcomes between the randomised treatment arms at endline. The analysis will follow the intention-to-treat approach as protocol and as treated, using econometric analysis for all the relevant outcomes of the intervention. Following Bruhn and McKenzie, impact will be assessed for the different treatment arms using both a ‘difference-in-difference’ (DID) estimator and a single difference analysis of covariance (ANCOVA) model [14].

The DID estimate is calculated as the average change in the outcome of interest (*Y*) in the treatment arm (*T*) minus the change in outcome in the control group (*C*), or:$$ {\Delta}^{DID}=E\left[\left({\overline{Y}}_1^T-{\overline{Y}}_0^T\right)-\left({\overline{Y}}_1^C-{\overline{Y}}_0^C\right)\right]. $$

A difficulty of DID analysis is serial correlation [15] resulting from unobserved factors affecting the outcomes that are themselves correlated over time and that produce auto-correlated errors and invalid standard errors. Serial correlation affects estimated standard errors and can lead to erroneous acceptance or rejection of null hypotheses but not the estimation of the effect size of the intervention. Thus, it may lead to erroneously finding or not finding a statistically significant impact of the intervention. Angrist and Pischke illustrate how this problem can be addressed by calculating clustered standard errors [16], a procedure that is easily implemented using Stata software. Clustered standard errors will also be employed in all cases in which correlated outcomes are observed within the same unit of analysis. For example, when the impact of the intervention is analysed at the school level and test scores within school are obviously correlated. Similarly, clustered standard error will be used at the household level when the project is affecting more than one child within the same family, as in the case of impact on younger siblings.

The single difference model specification has the following form:$$ {Y}_{i1}={\beta}_0+{\beta}_1{T}_i+{\beta}_2{Y}_{i0}+{\varepsilon}_i, $$

where *Y*_*i*0_ is the outcome variable at baseline, *Y*_*i*1_ is the outcome variable at endline and *T*_*i*_ is a dummy variable for the treatment. The ANCOVA estimator has been shown to provide a more efficient estimate of programme impact when auto-correlation of outcomes is low [14].

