### Markets

Early studies of food prices in Ghana found negligible price differences across the country [18]. Regional equality of consumer prices, however, does not imply the equality of producer prices at a more localised level. The ability of market interventions to influence local price dynamics depends on the level of spatial market integration between local markets. Abdulai [19] analysed the maize market in Ghana and found a high level of integration, meaning a quick transmission of prices from one locality to the other. In these circumstances large purchases of staple food in localised markets are unlikely to produce price changes. Cudjoe et al. tested for market integration for several staple foods in Ghana and found a high level of integration for rice and maize but much less for tubers such as cassava and yam [20]. Prices of the latter items may be strongly localised and transmission between markets may not be easy. It should also be noted that the studies quoted above looked at market integration across large wholesale markets that are well-connected by roads and communication flows. Differences in prices might emerge in more remote and isolated areas even for more commercial crops like maize and rice. We therefore considered studying the impact of the intervention on local market prices, particularly when the food purchased consists of food items that are not highly commercialised such as cassava and yam.

Impact on prices could, in principle, be observed through the household-level questionnaires. The farm gate price could be observed at the household level by including in the questionnaire questions related to prices paid and time of sales. This, however, would complicate the income section of the farmer questionnaire. Consumer prices are more difficult to observe in a standard household survey because the recall time is 7 or 30 days and there is only one survey per year. As part of the programme monitoring activities, price data will be collected, on a monthly basis, for main staple crops in the local market next to each of the selected schools for a sub-sample of farmer households. Collection of prices does not even require visits to markets if stable contacts can be established with collectors in each of the markets and prices could be communicated by phone.

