### Data collection

The enumerators were recruited from Noguchi Memorial Institute for Medical Research (NMIMR) and Institute of Statistical, Social and Economic Research (ISSER), and trained for the baseline survey. Each team, led by a supervisor and assisted by community leaders conducted household listings and sampling in each enumeration area (EA). Maps were obtained for most of the EAs from the Ghana Statistical Service. The EA maps made it possible to identify all dwelling structures within a geographical space with a well-defined boundary. All dwelling/housing structures within each EA were serially numbered to facilitate the complete listing of households. The list of households in each EA constituted the sampling frame from which participating households were selected at random for the interview. A total of 2626 households in 116 communities were surveyed (see Table 5 for the data collection coverage) between the 22 June and the 2 September 2013.

**Table 5 Tab5:** Household data collection coverage

Region	Communities	Number of households		
		Intervention	Control	Total
Western	8	96	80	176
Central	6	75	60	135
Greater Accra	2	24	25	49
Volta	10	123	101	224
Eastern	6	75	60	135
Ashanti	18	225	180	405
Brong-Ahafo	12	150	120	270
Northern	26	319	284	603
Upper East	10	225	179	404
Upper West	10	125	100	225
Total	116	1437	1189	2626

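### The only randomised endline falls outside the hunger months that the baseline fell in, so short-term food effects will be post-lean-season effects, and the HGSF+ v GSFP models carry no zone term to absorb seasonal differences

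*Protocol article*

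**What the plan says.** **Seasons.** Protocol, Country context: "Food security in the marginal agricultural and arid areas varies with the seasons". The same section continues "The peak hunger seasons for the south of Ghana are from May to August", and for the north gives "peak hunger seasons between July and October". It also reports that anaemia in school-aged children differs widely by ecological zone: 65 % in the northern savannah, 59 % in the coastal savannah and 16 % in the transitional zone.

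**Survey rounds.** Design of the randomised evaluation envisages two rounds, the second being "a follow-up planned in November 2015". Control schools enter the programme after that. Later surveys are only a possibility; they would use matched controls and are aimed at smallholder agriculture. Data collection dates the baseline fieldwork "between the 22 June and the 2 September 2013".

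**Allocation.** Study area and site selection randomises school feeding v control within a matched pair of schools in each district. HGSF+ v GSFP is allocated between districts, by choosing the permutation in which community- and district-level variables predict selection least.

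**Analysis.** Methods of analysis says "The DID estimate is calculated as the average change in the outcome of interest" in the treatment arm minus that in the control arm. The ANCOVA has the endline outcome on a treatment dummy and the baseline outcome. Neither formula has a zone or region term.

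**The concern.** Food security is part of the programme's purpose (Complex intervention, The HGSF pilot) and of how districts were prioritised (Study area and site selection). Yet no household or child outcome will be measured under a randomised contrast during the hunger months.

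The document itself gives reasons why effects could depend on season. The Complex intervention section reports price rises of up to 400 % between harvest and lean periods, says caterers cope by cutting quantity or adjusting menus, and suggests that buying from smallholders could soften price volatility. The last of these is what the HGSF agriculture component promotes. A November result could therefore differ from a lean-season result, for school feeding v control and for HGSF+ v GSFP alike. If the limit is not stated, a small November effect on diet may be read as a small effect over the year.

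The second issue is precision. HGSF+ v GSFP compares 29 districts with 29 others, and the zones have different hunger calendars. If the swing from baseline to November differs by zone, any north/south imbalance between the two sets of districts feeds into the estimate.

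**Working it through.** There is no stated figure to reproduce. The check is a date count, the algebra of the estimator, and an illustration.

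**1. Dates.** 22 June to 2 September is 9 + 31 + 31 + 2 = 73 days.
- Southern window (May to August): 9 + 31 + 31 = 71 of 73 days, 97 %.
- Northern window (July to October): 31 + 31 + 2 = 64 of 73 days, 88 %.
- November: 0 of 30 days in either window.

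These are shares of the fieldwork calendar. The article gives no fieldwork dates by zone.

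**2. Recall.** The article states no recall period for food consumption. The Markets section says "the recall time is 7 or 30 days and there is only one survey per year", but of consumer prices in a standard household survey. If 7 or 30 days did apply to food, and interviews were spread evenly over November, the recall days falling in October would be (7 + 6 + … + 1)/(30 × 7) = 28/210 = 13 %, or (30 + 29 + … + 1)/(30 × 30) = 465/900 = 52 %. In the north those days lie in the last month of the hunger window. In the south none reach the window.

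**3. School feeding v control.** Let both schools of a pair have baseline mean μ, a seasonal shift s and a programme effect τ. Then DID = [(μ + τ + s) − μ] − [(μ + s) − μ] = τ. The shift cancels, and it does so within each district, so zone-specific shifts cancel too. ANCOVA compares the arms at the same endline.

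**4. HGSF+ v GSFP.** Let p_H and p_G be the northern shares of districts in the two arms, s_N and s_S the zone shifts, and δ the true difference. Then

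DID = δ + (p_H − p_G)(s_N − s_S) + sampling error.

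Under random allocation p_H − p_G averages zero, so there is no expected bias. Its realised value is not zero in general, and that adds variance.

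**5. Illustration with assumed inputs, in arbitrary outcome units.** 58 districts, 23 of them northern, school-mean error SD 0.2 in each round, unrestricted split into 29 and 29, 4,000 simulated trials:

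| Assumed shift north / south | School feeding v control, mean (truth 0.20) | HGSF+ v GSFP, mean (truth 0) | HGSF+ v GSFP, SD |
|---|---|---|---|
| 0 / 0 | 0.200 | 0.001 | 0.073 |
| 0.5 / 0.5 | 0.200 | 0.001 | 0.075 |
| 1.0 / 0.3 | 0.200 | 0.000 | 0.119 |

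The algebra agrees. Sampling variance is (0.2² + 0.2²) × 2/29 = 0.0055, SD 0.074. The zone component is (1.0 − 0.3)² × [23 × 35/(58 × 57)] × 2/29 = 0.49 × 0.0168 = 0.0082. The total is 0.0137, SD 0.117. A zone-by-round term removes the second component.

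The number of northern districts is an assumption. The article does not define the north by region, and the community column of Table 5 sums to 108, not the 116 printed. Northern, Upper East and Upper West hold (603 + 404 + 225)/2626 = 47 % of households, which would correspond to about 27 of 58 districts. With 27 the zone component is 0.49 × [27 × 31/(58 × 57)] × 2/29 = 0.0086, which is almost the same.

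**The case against.** A reader might infer that DID is biased because baseline and endline fall in different seasons. The design does not support that. Both arms are surveyed in the same rounds, school feeding v control is paired within district, and HGSF+ v GSFP is randomised.

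A reader might also infer that every nutrition effect is a post-lean snapshot. That is too broad. Height-for-age reflects cumulative growth, November starts the day after the northern window closes, and the seasonality statement is confined to marginal agricultural and arid areas.

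Nor do the documents show that the endline should move. They give no school calendar, so it is unknown whether meals would be served in another window, and a move would change exposure and cost. Survey timing is a legitimate choice.

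The noise cannot be sized from the article. It gives no seasonal swing, and the restricted allocation may have balanced zones better than an unrestricted split. The balancing variables are not listed.

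Finally, model covariates are commonly left to an analysis plan. The article promises to control for group differences, foresees geographic sub-group analysis, and adds quarterly process monitoring and monthly prices. This stands, and it keeps the point modest. It does not remove it. Monitoring and prices are not child or household outcomes. A promise to adjust for baseline differences does not cover a zone-specific change between rounds. And the article does not mention the missing lean-season contrast.

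**Conclusion.** The point holds as a limit on what the trial can claim, together with a modest gain in precision. The dates come straight from the document: baseline almost wholly in the hunger months, the one randomised endline outside them, and no randomised control afterwards. For intake, dietary diversity and food expenditure there will be no randomised lean-season estimate. In the north this is softened if food recall is long enough to reach into October.

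Neither main contrast is biased in expectation. For HGSF+ v GSFP, zone-specific swings add variance that the DID and ANCOVA as written leave in. The rise in SD from 0.073 to 0.119 shows the mechanism under assumed shifts, and it is not an estimate for this trial. The true cost may be near zero if zones swing alike or if the allocation balanced them.

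**What to change.** 1. For HGSF+ v GSFP, add zone (or region)-by-round terms to the DID and zone (or region) to the ANCOVA, for food consumption, dietary diversity, expenditure, haemoglobin and BMI-for-age. Define zone before the endline data are analysed. The information is already held. The cost is one degree of freedom for a north/south term or nine for ten regions, among 58 districts. Zone is the safer choice: Greater Accra has two communities in Table 5, hence one district, and a region term would remove it from this contrast.
2. State that effects on short-term food outcomes refer to the post-lean season, and do not present them as annual or lean-season impact. State the food recall period alongside. This costs a sentence or two.

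The school feeding v control model needs no change on this account.

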### Random assignment and manipulation of treatments

Households and schools were randomly assigned to three treatment arms:Control group: these are schools and households from communities where the intervention will not be implemented. The intervention will be delayed by at least 3 years in these communities, preferably without informing schools and households. After the 3- year period, these schools will be covered by the GSFP.Regular GSFP group: these are schools and communities where the standard GSFP is implemented, with caterers responsible for the food procurement and preparationHGSF+ group: these are schools and communities where the programme is implemented in addition to a pilot capacity-building component, including training of community-based organisations and other stakeholders, on food procurement, nutrition education, and feedback monitoring. This group will be randomly divided into two sub-groups (HGSF+ and HGSF++) as part of a study focussing on anaemia.

Note that the HGSF+ intervention will be conducted at the district level. Training and monitoring systems involve caterers and exert their effects at the district level, affecting outcomes in schools where the HGSF+ programme is not implemented. On the other hand, the number of districts where the programme is implemented is rather small, which reduces the statistical power of the analysis, and the effects of the school feeding intervention against the control group are best observed at the school level. Hence, we opted for a design that compares the outcomes of the school feeding and control groups at the school level, and that compares outcomes of HGSF+ and regular school feeding (GSFP) at the district level.

The GSFP selected 58 districts in which the programme will be implemented. In each of these districts, two candidate schools were selected and each school was randomly assigned to the treatment or to the control. A protocol was designed in order to ensure that the schools were comparable based on data from the Education Management Information system (EMIS) and that contamination between the two schools in each district will be minimised. This will allow comparison of outcomes of the intervention against the control group at the school level in 58 districts. The 58 schools assigned to the intervention were then randomly assigned to regular GSFP and HGSF+. In this way the randomisation of the HGSF+ intervention occurs at the district level. The number of 58 schools is based on power calculations (see Appendix 1) determined with the objective of achieving statistical validity and representativeness for the main outcomes of interest.

### Anaemia sub-study

The impact evaluation includes a sub-study focussing on nutrition in school feeding with and without micronutrient fortification. A sub-group of 14 of the 29 HGSF+ groups was randomly assigned to receive food fortification (the HGSF++ group) in addition to training and sensitisation activities that are part of the HGSF+ pilot (see Fig. 3). Data will be collected from children aged 5–15 years in the HGSF++, HGSF+, GSFP and control communities. Targeted schools were surveyed as part of the broader impact evaluation baseline.

**Fig. 3 Fig3:**
[figure not shown]
Schematic view of the design of the randomisation

### Sample sizes

For the impact evaluation, power calculations and resource availability suggested the adoption of a sample of 25 households from the communities in the areas of the 58 schools receiving the intervention and of 20 households in the communities of the 58 control schools.

Households were randomly selected from household listings in the catchment areas of the selected schools for the survey interviews. The household listings were stratified into farmer/non-farmer households, based on agriculture classification data from the national census. Farmer households were sampled in both areas in the following way: 10 out of the 25 households in the 60 intervention communities were farmer households and 5 out of the 20 households in the 60 control communities were farmer households. Non-farmer households with children in the 5–15 years age group were randomly selected from the household listings. This distribution of the sample between farmer and non-farmer households and between project control groups allows the construction of comparable samples (see Table 2).

**Table 2 Tab2:** Sample sizes

	Districts	Schools	Households with children in the 5–15 years age group	Farmer HH	Children^a^
Control	58	58	870	290	2375
GSFP	29	29	435	290	1383
HGSF+	29	29	435	290	1383
(HGSF++)	(14)	(14)	(210)	(140)	(668)
Total	58	116	1740	900	5142

^a^the number of children is an estimate based on an average of 2.28 children per family in families with children and 1.35 children per family in farmer households

*GSFP* Ghana School Feeding Programme, *HGSF* ‘home-grown’ school feeding, *HH* households

In each household, all children aged between 5 and 15 years were asked education outcome-related questions (enrolment, attendance, drop-out) and were tested in literacy, maths, forward and backward digit span and Raven-like matrices. Anthropometry and haemoglobin level measurements were administered to children aged 5–15 years. Anthropometry indicators were also be measured for children aged 2–5 years. As each school is assigned a caterer by the GSFP programme, the sample also included 58 caterers who were interviewed using a semi-structured questionnaire.

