Haemoglobin levels (g/dL)	714	11.3 [1.34]	422	11.3 [1.35]	169	11.3 [1.36]	32	11.4 [1.47]	91	11.3 [1.21]	0.9088	0.8764	0.8469
Total maize production volumes (kg)	2626	787 [1751]	1163	864 [2034]	722	807 [1596]	375	590 [1248]	366	702 [1478]	0.0439	0.0376	0.2646
Total rice production volumes (kg)	2626	141 [652]	1163	149 [700]	722	148 [645]	375	137 [678]	366	111 [449]	0.6003	0.4551	0.5297
Total maize sale volumes (kg)	2626	393 [1196]	1163	432 [1261]	722	446 [1337]	375	270 [880]	366	292 [907]	0.1381	0.0057	0.7435
Total rice sale volumes (kg)	2626	84 [484]	1163	94 [583]	722	87 [413]	375	70 [397]	366	61 [327]	0.3509	0.2895	0.7286
Other variables													
Age (for 15 years and younger)	8407	7.5 [4.2]	3153	5.8 [9.0]	1918	6.2 [9.5]	942	6.2 [9.3]	917	6.1 [9.9]	0.057	0.847	0.8071
Is a girl? (for 15 years and younger)	8407	0.48 [0.5]	3799	0.48 [0.50]	2318	0.49 [0.50]	1167	0.47 [0.50]	1123	0.51 [0.5]	0.4933	0.9377	0.0989
Birth order (for all children)	8533	2.9 [2.0]	3791	2.9 [2.1]	2397	3.0 [2.0]	1189	3.0 [2.0]	1156	2.9 [1.9]	0.8275	0.021	0.2204
Is enrolled in school? (for 5–15 years)	6178	0.92 [0.27]	2755	0.91 [0.29]	1737	0.92 [0.26]	852	0.94 [0.01]	834	0.91 [0.29]	0.0375	0.9395	0.0065
Receives free school meals?	6280	0.19 [0.39]	2809	0.17 [0.38]	1768	0.23 [0.42]	860	0.13 [0.34]	843	0.24 [0.43]	0.0001	0.0055	<0.001
Distance to nearest school	6343	0.47 [3.24]	2765	0.45 [3.14]	1808	0.58 [4.34]	891	0.21 [0.85]	879	0.59 [2.29]	0.597	0.0992	<0.001
Time to school	6333	21.4 [45.6]	2778	19.6 [31.3]	1796	18.8 [32.5]	888	17.6 [22.7]	871	35.9 [95.1]	0.007	<0.001	<0.001
Total education expenditure	5635	23923 [35642]	2410	19250 [30878]	1640	27089 [37899]	789	25732 [37096]	796	29752 [40791]	<0.001	0.6249	0.0403
Mother’s education level (5–15 years)	5096	5.9 [9.4]	2290	5.7 [9.1]	1437	6.1 [9.6]	690	6.1 [9.4]	679	6.0 [9.8]	0.1946	0.8518	0.7608
Education level of head of household	2626	1.4 [2.6]	1163	1.4 [2.7]	1463	1.3 [2.5]	375	1.6 [2.7]	366	1.3 [2.2]	0.9393	0.2147	0.1344
Household size	2626	5.7 [2.4]	1163	5.7 [2.4]	722	5.8 [2.4]	375	5.7 [2.3]	366	5.6 [2.3]	0.8747	0.1774	0.5572
Per-capita expenditure quintile	2625	3.1 [1.4]	1162	3.2 [1.4]	722	2.9 [1.4]	375	3.3 [1.4]	366	3.1 [1.4]	0.1763	0.0008	0.2199
Household expenditure on food	2626	3473 [2187]	1163	3483 [2213]	722	3370 [2254]	375	3502 [1846]	366	3608 [2289]	0.815	0.1041	0.4874
Household expenditure on health	2626	93.5 [112]	1163	97.7 [116]	722	88.7 [107]	375	93.3 [108]	366	90.0 [112]	0.0894	0.595	0.6768

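### Farmer households are 40% of the intervention sample but 25% of the control sample, so pooled school feeding v control comparisons need a stratum term or weights that the stated models lack

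*Protocol article*

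**What the plan says.** Under Sample sizes, the protocol article sets "a sample of 25 households from the communities in the areas of the 58 schools receiving the intervention and of 20 households in the communities" around the control schools. Sampling was by stratum: "The household listings were stratified into farmer/non-farmer households, based on agriculture classification data from the national census". The number of farmer households depends on the side. For the intervention side the text gives "10 out of the 25 households in the 60 intervention communities were farmer households"; for the control side it gives "5 out of the 20 households in the 60 control communities were farmer households". The section then states that "This distribution of the sample between farmer and non-farmer households and between project control groups allows the construction of comparable samples".

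The footnote to Table 2 estimates child numbers from "an average of 2.28 children per family in families with children and 1.35 children per family in farmer households".

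Methods of analysis rests the causal claim on "comparisons of mean outcomes between the randomised treatment arms at endline". It names two estimators: a difference-in-difference (DID) of arm means, and an ANCOVA whose equation contains an intercept, the treatment dummy and the baseline outcome. Multi-level models with unnamed covariates follow as robustness checks. The Abstract and the Discussion promise to control for differences across groups in outcome and control variables. The Results section lists SF (GSFP and HGSF combined) v control as one of the main evaluation comparisons.

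**The concern.** Randomising schools balances the communities. It does not balance the households drawn from them if the sampling rate itself depends on the arm. Here the pooled samples differ in farmer share by design, and would still differ with any number of clusters.

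An outcome that differs between farmer and non-farmer households will then show a pooled SF v control difference at endline even if the programme does nothing, unless the analysis accounts for the stratum. Household income, production and sales are primary indicators in Table 1 and are the natural candidates. The strata also differ in make-up: non-farmer households had to have children aged 5–15, no such condition is stated for farmer households, and the planning factors are 2.28 against 1.35 children per household.

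The same mixing affects the reading of Table 6. The Discussion concludes from its tests that random allocation did not give comparable groups, but the SF v control column combines allocation with arm-dependent sampling.

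**Working it through.** **1. Reproduce Table 2.** Each control community has 15 non-farmer and 5 farmer households; each intervention community has 15 and 10.

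- Control: 58 × 15 = 870; 58 × 5 = 290; children 870 × 2.28 + 290 × 1.35 = 2375.1 (printed 2375).
- GSFP, and likewise HGSF+: 29 × 15 = 435; 29 × 10 = 290; children 1383.3 (printed 1383).
- HGSF++: 14 × 15 = 210; 14 × 10 = 140; children 667.8 (printed 668).

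The arm rows reproduce. The printed farmer total of 900 does not: 290 + 290 + 290 = 870. The figure 900 is 60 × 5 + 60 × 10, which follows from the 60 communities per side in the sampling sentence instead of 58.

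**2. Farmer share by side.**

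- Households: 10/25 = 0.40 against 5/20 = 0.25; difference 0.15.
- Children: 13.5/(34.2 + 13.5) = 0.283 against 6.75/(34.2 + 6.75) = 0.165; difference 0.118.

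**3. Bias with no programme effect.** Let d be the farmer minus non-farmer gap in the outcome, in SD. The documents do not give d, so 0.1 to 1.0 is assumed.

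- Raw endline means: share difference × d.
- ANCOVA as written: roughly share difference × d × (1 − ρ), where ρ is the within-arm correlation of baseline and endline.
- DID: share difference × the change in d between rounds, which is zero if d is constant.

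| d (SD) | Household, raw | Household, ANCOVA (ρ = 0.5) | Child, raw | Child, ANCOVA (ρ = 0.5) |
|---|---|---|---|---|
| 0.1 | 0.015 | 0.007 | 0.012 | 0.006 |
| 0.5 | 0.075 | 0.037 | 0.059 | 0.030 |
| 1.0 | 0.150 | 0.075 | 0.118 | 0.059 |

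For scale, the Appendix gives a 120-cluster detectable difference of 0.21 SD for Raven's scores.

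**4. Simulation check.** 58 + 58 communities, household sample as above, no programme effect, 400 runs. Assumed: between-community variance 0.10, and half of the remaining variance persistent between rounds.

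| Gap | Raw | ANCOVA | DID | ANCOVA + stratum |
|---|---|---|---|---|
| 0.5 SD, constant | 0.077 | 0.035 | 0.002 | 0.003 |
| 1 SD, constant | 0.145 | 0.052 | −0.002 | −0.003 |
| 1 SD, widening by 0.25 SD | 0.192 | 0.089 | 0.039 | 0.003 |

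ANCOVA does better than step 3 at the 1 SD gap because persistent community effects and the gap itself raise the baseline–endline correlation. The stratum term brings the bias to about zero in every case.

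**5. What Table 6 tested.** Rebuilding the SF v control p-values from the printed n, mean and SD, as ordinary two-sample t-tests on all 2626 households, gives 0.0435 for maize production (printed 0.0439), 0.1375 for maize sales (0.1381) and 0.088 for health expenditure (0.0894). The column is consistent with pooled, unweighted, unstratified tests.

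**6. Direction.** Mean maize production is 864 kg in control. In SF it is (722 × 807 + 375 × 590 + 366 × 702)/1463 = 725 kg, a difference of −139 kg. Suppose non-farmers produce a fraction r of what farmers do (assumed), and set both sides to a common 32.5% farmer share. SF becomes 725 × (0.325 + 0.675r)/(0.40 + 0.60r), and control 864 × (0.325 + 0.675r)/(0.25 + 0.75r). The difference is −139 kg at r = 1, −230 kg at r = 0.5 and −534 kg at r = 0. For this variable the mix would hide part of a difference, not create one.

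**The case against.** The strongest reply has four parts.

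- **The sentence has a sound reading.** There are 870 non-farmer households on each side and 290 farmer households in each of control, GSFP and HGSF+. Within stratum the samples are comparable. This stands, but the sentence carries no such limit and pooled SF v control is a main comparison.
- **DID is planned, and it cancels a constant gap.** This stands. The exposure is mainly in endline means and ANCOVA, and in DID only if the gap moves.
- **Adjustment is promised, and the article is condensed.** The ANCOVA equation is a general form, and an analysis plan that is not shown may hold weights or covariates. This stands in part. The promise concerns observed baseline differences, which the Discussion puts down to sampling error; farmer status is not a row of Table 6, so the promise need not reach it.
- **Farm income may be meant for farmers only.** The Abstract names smallholder farmer income, and the Appendix assumes 20 farmers per community. This is likely, and such an analysis has no composition bias. But Table 1 says household income, production and sales, and Table 6 shows production and sales over all households.

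A reader might infer that every SF v control result will be biased, or that farm income will show a large spurious gain. The documents support neither. DID and within-farmer estimates escape, and any percentage would rest on an assumed farmer/non-farmer income ratio applied to a pooled outcome that may not be the one analysed. Nor can the printed maize difference be blamed on the mix: it runs the other way.

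**Conclusion.** The point holds in a limited form. The 40% v 25% mix is exact and comes from the sampling design, not chance. No stated model accounts for it, and the claim of comparable samples is true only within stratum. Pooled endline means are exposed to a bias of 0.15 × the gap (household) or about 0.12 × the gap (child). ANCOVA as written removes only part, and DID removes all of it if the gap is constant.

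Size and sign are unknown because the documents report no outcome by farmer status; the SD figures rest on the assumed range of 0.1 to 1.0. The child shares rest on the planning factors under Table 2. Analyses within the farmer stratum are unaffected, as are GSFP v HGSF and HGSF+ v HGSF++, where the planned share is 40% throughout. This is a nearly free improvement to the analysis, not evidence that the trial's main results will be wrong.

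**What to change.** 1. Add the farmer/non-farmer sampling stratum to every pooled SF v control model, or weight each stratum by its share in the community household listing. In ANCOVA a stratum indicator is enough. In DID the stratum must be interacted with survey round, since a fixed gap already cancels and only a changing one does harm.
2. State that farm income, production and sales are estimated among farmer households.
3. Redo the SF v control column of Table 6 with stratum adjustment before attributing imbalance to the random allocation.
4. Reword the sentence under Sample sizes to say that the samples are comparable within stratum, and that pooled SF v control comparisons are stratum-adjusted or weighted.
5. While editing, reconcile 58 with 60 communities and the farmer total of 900 with 870.

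The stratum was fixed at sampling and the listings exist, so no new data are needed. The cost is one variable in the models, or one set of weights, and a rerun of one table column.
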